### Study population

#### Inclusion criteria

To determine the composite primary outcome of time to death or first-time care at home or paid care support for the first time within 90 days after the index event, we will use routine data from three cooperating health insurance companies (AOK Nordost, BARMER, TK). For this purpose, eligible study participants must (1) have continuous health insurance with one of these health insurers during the evaluation period, (2) be admitted during the intervention or control period to one of the cooperating regional hospitals, (3) have a neurological diagnosis (International Classification of Diseases (ICD)-10 main diagnosis) such as stroke (I60–64), status epilepticus or impaired level of consciousness (G41, R40), meningitis /encephalitis (A82.0–2, A85–87, G00–03, G06–09), acute spinal cord injury (S14, S24, S34, G82), (4) and be over 18 years of age of both sexes.

We had originally planned to include patients diagnosed with traumatic brain injury (S06–07) in an earliert version of the study protocoll. However, since patients with traumatic brain injury are only rarely managed by our project partners in the participating regional hospitals they are not included in the primary study population, but rather as a companion study population in a sensitivity analysis.

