### Statistical analyses

#### Primary analysis

Because health insurance data will be provided anonymously, we cannot determine the effect of telemedicine consultation on an individual patient level. Rather, we will evaluate the effects of the ANNOTeM concept in clusters. The primary outcome will be analysed as the time from the index visit to the occurrence of the compound outcome as described above. Separate Cox models will be fitted for eligible patients insured at the cooperating health insurance companies, admitted and treated in both, the pre-implementation period and the intervention period. Cox models will comprise sex (m/f only), age and co-morbidity (Y/N) as covariates. Hazard rate ratios will be used to compare time-to-compound event between the two periods. All tests will be performed at a significance level of alpha = 0.05, adjusted for two-sided testing and the k = 6 tests of the primary and secondary analysis. All tests will be performed using the statistics package ‘R’ (version 3.6).

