### Data collection, management, and analysis

#### Data collection methods

The health insurance data for determining the defined outcomes are provided by the cooperating statutory health insurance companies (AOK Nordost, BARMER, TK) in accordance with the defined inclusion criteria. Within the framework of ANNOTeM, pseudonymised personal data of the health insurances will be transmitted in accordance with §75 Social Security Code V to a third trust party, which forwards the data in anonymised form to the evaluating institute. This forwarding has been approved by the supervisory authorities of the participating health insurance companies.

In addition to the account data for identifying the defined outcomes and costs, basic data on age and sex, insurance status and paid nursing care or nursing home care are provided at the beginning of observation.

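### The primary Cox model does not adjust or stratify for insurer, so a change in insurer mix between the periods could enter the hazard ratio

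*Protocol article*

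**What the plan says.** Under Inclusion criteria, the article bases the primary outcome on three insurers' data ("we will use routine data from three cooperating health insurance companies (AOK Nordost, BARMER, TK") and requires each patient to "have continuous health insurance with one of these health insurers during the evaluation period". Under Data collection methods, the outcome data come from the same source: "The health insurance data for determining the defined outcomes are provided by the cooperating statutory health insurance companies". The baseline fields come with them: "basic data on age and sex, insurance status and paid nursing care or nursing home care are provided at the beginning of observation". Two of the three endpoint components under Primary outcomes, nursing home care and paid outpatient nursing care, are therefore read from insurers' benefit records.

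Under Primary analysis, the contrast is before against after: "Hazard rate ratios will be used to compare time-to-compound event between the two periods". The covariate list is stated outright: "Cox models will comprise sex (m/f only), age and co-morbidity (Y/N) as covariates". No insurer term or stratum is named there, in the Secondary analysis or in the Sensitivity analysis. One sentence is unclear on this point: "Separate Cox models will be fitted for eligible patients insured at the cooperating health insurance companies, admitted and treated in both" of the two periods. It does not say whether the separate fits are by period, insurer or diagnosis.

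Data collection methods also says that a trust party passes the data to the evaluating institute in anonymised form. It does not say whether an insurer identifier is kept.

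**The concern.** Nothing in the design balances insurer between the periods. The comparison is not randomised. The control window runs from 16 November 2014 to 31 May 2017 and the intervention window from November 2017 to 31 July 2020, so their midpoints lie about three years apart. Insurer marks both which population a patient belongs to and which administrative system recorded the care events, and a single yes/no co-morbidity term is a coarse control for differences between memberships.

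Table 1 gives one concrete route by which the mix could move. All eleven hospitals share one control window, but their recruitment starts range from 16 November 2017 to 10 February 2019. Early-starting hospitals therefore weigh more in the intervention group than in the control group. If insurer shares differ by hospital, the pooled mix shifts even when no hospital's own mix changes.

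At stake is whether part of the period hazard ratio reflects who was insured where, and not the network. The Limitations text acknowledges time trends in care but does not mention insurer mix.

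**Working it through.** **Inputs from the article.** Event rates of 39% (control) and 32% (intervention), and at least 1820 patients per group (Sample size calculation); k = 6 tests (Primary analysis). The 1820 is taken as stated; whether it matches the stated power is a separate matter and is not used here.

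**Inputs that are assumptions.** The article gives no insurer shares and no insurer-specific rates. Assume one insurer's members have hazard h = 1.2, 1.3 or 1.5 relative to the others after adjustment, and that their share falls from p0 = 0.60 to p1 = 0.55 or 0.50. Patients are treated as independent and there is no true effect.

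**Planned effect.** HR = ln(0.68)/ln(0.61) = 0.780; log HR = -0.248.

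**Spurious log HR.** b = ln[(1 + p1(h - 1))/(1 + p0(h - 1))].

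**Standard error under the null.** Events per group 0.39 x 1820 = 709.8; SE = sqrt(2/709.8) = 0.053.

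**False-positive rate, both tails.** Phi(-z - b/SE) + 1 - Phi(z - b/SE), with z = 1.960 at 5% and z = 2.638 at 0.05/6 (Bonferroni assumed).

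| h | share | ratio inside ln | b | spurious HR | share of -0.248 | at 5% | at 0.05/6 |
|---|---|---|---|---|---|---|---|
| 1.2 | 60% to 55% | 1.110/1.120 | -0.009 | 0.991 | 4% | 5.3% | 0.9% |
| 1.2 | 60% to 50% | 1.100/1.120 | -0.018 | 0.982 | 7% | 6.3% | 1.2% |
| 1.3 | 60% to 55% | 1.165/1.180 | -0.013 | 0.987 | 5% | 5.7% | 1.0% |
| 1.3 | 60% to 50% | 1.150/1.180 | -0.026 | 0.975 | 10% | 7.7% | 1.7% |
| 1.5 | 60% to 55% | 1.275/1.300 | -0.019 | 0.981 | 8% | 6.6% | 1.3% |
| 1.5 | 60% to 50% | 1.250/1.300 | -0.039 | 0.962 | 16% | 11.4% | 2.9% |

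**Direction.** Reversing the shares reverses the sign: for h = 1.5 and a share rising from 50% to 60%, b = ln(1.300/1.250) = +0.039, HR 1.04, which works against the intervention.

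**Second method.** A two-class exponential mixture with the control rate held at 39%, and the higher-risk share falling from 50% to 45% or 40%, gives a spurious HR of 0.989 or 0.978 for an insurer HR of 1.25, and 0.980 or 0.960 for 1.5. With an insurer HR of 2.0 it gives 0.966 or 0.933, with false-positive rates of about 10% to 25% at 5% and 2.3% to 8.6% at 0.05/6. With no residual insurer difference (HR 1.0) it is 1.000 for any shift.

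**Size of the Table 1 route.** Six hospitals start by the end of March 2018 (BER, LUD, NAU, LUC, STR, TEM). Their days to 31 July 2020 sum to 941 + 988 + 988 + 986 + 861 + 854 = 5618. The other five (KYR, RAT, UEC, GAR, PRE) give 623 + 574 + 564 + 537 + 564 = 2862. The early six hold 5618/8480 = 66% of intervention hospital-days but 6/11 = 55% of control hospital-days. If an insurer's share differed by 20 points between early and late hospitals (assumed), the pooled mix would move by 20 x (0.662 - 0.545) = 2.3 points. With h = 1.5, b = ln(1.2885/1.300) = -0.009. This route alone is small.

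**Precision under stratification.** Expected events are 709.8 + 0.32 x 1820 = 709.8 + 582.4 = about 1,292 over three strata, so the loss is negligible.

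**The case against.** The strongest reply is that the confounding is only hypothesised. Bias needs both a change in insurer shares and a residual difference between insurers, and the article reports neither. That stands, and it limits what can be claimed. A reader might infer that the hazard ratio is biased, or that insurers grant or record care differently; nothing in the article says so.

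A reader might also take 11.4% as the error rate of the planned test. It is not. It belongs to the most extreme assumed scenario and uses a nominal 5% level, whereas the article adjusts for six tests. If that adjustment is Bonferroni, every scenario in the table stays below 3%.

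Three further replies hold in part. First, the sentence on separate models does not exclude fits by insurer, so it cannot be said that the plan imposes one baseline hazard on all three. Second, it is not established that the analyst will hold an insurer code; the listed field is insurance status. Third, it is tempting to extend the point unchanged to the comparison with non-network hospitals. There the test is an interaction, using the same insurers, region and periods. Stable differences in mix do not bias it and a region-wide shift largely cancels; only a differential change would matter. That comparison is secondary, however, and does not correct the primary hazard ratio.

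Finally, an insurer stratum could be called detail for an analysis plan that is not shown. This carries less weight, because the article does not leave the covariates open: it lists them.

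**Conclusion.** The point holds as a cheap improvement to a stated model, not as a demonstrated error. The covariate list omits a grouping inherent in the data sources, in an unrandomised before/after contrast where two endpoint components are insurer records. Under moderate assumptions the distortion is 4% to 16% of the planned log hazard ratio, in either direction. It would become material only with larger insurer differences or larger shifts. All these sizes rest on assumed insurer shares and hazards and on independent patients, since the article supplies no insurer figures.

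**What to change.** - Have the trust party keep a three-level insurer code in the anonymised data, and confirm that it will reach the evaluating institute.
- State what the separate Cox models are. If fits by insurer are meant, say so and say how the results are combined.
- Fit the primary Cox model with a period term, the listed covariates and insurer as a stratification factor, so that each insurer has its own baseline hazard.
- Report insurer shares by period, so that readers can see whether the mix moved.
- Stratify the network-by-period comparison by insurer in the same way, as protection against a differential change in mix.

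The cost is one line in the model specification, plus retention of the code, which may need agreement under the data-protection arrangements. If the code cannot be kept for individual records, insurer shares by period should still be requested from the insurers.

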#### Secondary analysis

The secondary analysis compares the survival rates obtained in the primary for the network clinics with the group of non-cooperating hospitals using the log-rank-test for 2 × 2 factorial designs (control vs intervention period and network vs non-network hospitals). A treatment effect will be revealed by a significant interaction in favour of the network clinics during the intervention period.

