#### Comparison with non-participating hospitals

In order to investigate whether differences in outcome in the cooperating hospitals may be caused by temporal trends, the composite primary outcome will also be analysed for the same two periods in patients fulfilling the identical inclusion criteria but being treated in hospitals of the same region that do not participate in the network (non-network community hospitals). The non-network hospitals were matched according to geographical location, size and amount of acute neurological cases per year. Data for this comparison are also provided by the three insurance companies.

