We acknowledge several limitations of the study: Changes in the care of patients with effects on the primary outcomes measured here may occur independently of study design through health policy measures and health care innovations. This can result in an overestimate of improved care for the intervention group compared to the pre-implementation control group. In order to control for this possible time trend, we have introduced a parallel control group of patients treated in non-network hospitals. A further limitation is that the definition of part of the composite outcome is based on routine data of the health insurances. It is possible that patients or their relatives do not apply for home care support provided by the health system even when they have a respective need of assistance. In addition, the decision for home care also depends, among other things, on the available social support at home or personal preferences. However, previous analyses have shown that the parameters of care support and home care correlate well with the degree of disability [18]. The approach taken in this project will be evaluated in the setting of the German health care system and results can therefore not be generalized.

On the other side, the study has several important strengths. First, the total number of patients treated in the hospitals with regard to the main diagnoses is recorded on the basis of health insurance data. Thus, the bias of patient selection by informed consent procedures often present in clinical studies is minimized. Second, study outcomes are assessed independently. Third, the combination of data collected within the telemedicine consultations along with quality management of the health insurance data provide the opportunity to evaluate the effects with a direct link to the health care context.

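### The period-by-network comparison rests on a log-rank-type test that is unadjusted, ignores hospital and gives no effect size; an adjusted Cox interaction model would serve it better

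*Protocol article*

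**What the plan says.** The primary analysis compares the network hospitals before and after implementation. For it, the Primary analysis section states: "Cox models will comprise sex (m/f only), age and co-morbidity (Y/N) as covariates". The same section explains that individual receipt of teleconsultation cannot be identified, and continues: "Rather, we will evaluate the effects of the ANNOTeM concept in clusters". It lists no hospital term and no method for clustering.

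The controlled comparison is in the Secondary analysis section: "The secondary analysis compares the survival rates obtained in the primary for the network clinics with the group of non-cooperating hospitals using the log-rank-test". The full phrase for the test is "using the log-rank-test for 2 × 2 factorial designs (control vs intervention period and network vs non-network hospitals"), with this decision rule: "A treatment effect will be revealed by a significant interaction in favour of the network clinics during the intervention period". The section names no interaction statistic, covariate, hospital term or effect measure.

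The section Comparison with non-participating hospitals gives the purpose: "In order to investigate whether differences in outcome in the cooperating hospitals may be caused by temporal trends". It describes how the comparators were chosen: "The non-network hospitals were matched according to geographical location, size and amount of acute neurological cases per year". The Discussion says of changes in care that are unrelated to the project: "This can result in an overestimate of improved care for the intervention group compared to the pre-implementation control group". It presents the parallel non-network group as the control for such a trend.

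**The concern.** The before-after comparison cannot separate the intervention from secular change, as the Discussion concedes. The period-by-network contrast is the only planned analysis that can, so any causal reading of the trial depends on it although it is labelled secondary.

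The named method is weak for that task in four respects.

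- **Target.** An ordinary log-rank test compares event curves between groups. Across four cells it responds to any difference. Stratified by one factor, it tests the main effect of the other. Neither is an interaction, and the article does not identify the factorial version it means.
- **Adjustment.** The hospitals are matched on location, size and case volume, not on patients. If the patient mix shifts differently over time in the two hospital groups, an unadjusted interaction absorbs that shift.
- **Hospital.** A log-rank-type variance treats patients as independent. Outcomes that drift differently from hospital to hospital add variance which the test does not see.
- **Estimate.** A p-value alone does not say how much of the before-after difference remains once the trend is removed.

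**Working it through.** The article gives no sample size, power or error rate for this comparison, so there is no figure of the plan's to reproduce. The checks below ask what each test targets and what ignoring hospital costs.

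**1. What is tested.** Let λ be the hazard in a cell, with N = network, C = non-network, 0 = control period and 1 = intervention period. The interaction is

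θ = log λ(N1) − log λ(N0) − log λ(C1) + log λ(C0).

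θ = 0 means that both hospital groups changed by the same hazard ratio. A four-group log-rank test has the null hypothesis that all four hazards are equal. A log-rank test of network stratified by period has the null hypothesis of no network difference. Neither null hypothesis is θ = 0.

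**2. Cost of ignoring hospital, for a test that does target θ.**

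Inputs from the article:
- 39% events in the control period and 1820 patients per group (Sample size calculation)
- 11 network hospitals (Structure of the network)

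Assumptions, because the article gives no figures:
- 1820 patients in each non-network cell as well, and 11 non-network hospitals
- hospitals of equal size
- hospital-by-period SD σ on the log hazard of 0.10, 0.15 or 0.20
- no effect of any kind, 39% in all four cells

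Events per cell: 0.39 × 1820 = 710.

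Variance of the θ estimate with patients treated as independent: 4/710 = 0.00564.

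Extra variance from hospital-by-period effects: 4σ²/11. Stable hospital differences largely cancel, because the same hospitals contribute to both periods.

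The true SE divided by the SE used is r = √[1 + (4σ²/11)/0.00564]. A nominal 5% test then rejects with probability 2[1 − Φ(1.96/r)].

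| σ | 4σ²/11 | r | Rejection by formula | Rejection by simulation |
|---|---|---|---|---|
| 0.10 | 0.00364 | 1.28 | 12.7% | 11.5% |
| 0.15 | 0.00818 | 1.57 | 21.1% | 21.3% |
| 0.20 | 0.01455 | 1.89 | 30.0% | 31.7% |

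The simulation used exponential times censored at 90 days, a stable between-hospital SD of 0.20 and 600 runs per row. It agrees with the formula. Without hospital variation, the same interaction contrast rejected in 4-6% of 1000 runs in each of five no-effect scenarios, so the excess comes from the ignored hospital-by-period variance.

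**3. At an adjusted alpha.** The Primary analysis section adjusts for k = 6 tests without naming a method. If this is Bonferroni (an assumption), alpha is 0.05/6 = 0.83%. The simulated false-positive rates are then 4.2%, 8.3% and 16.3%, about 5 to 20 times the nominal level.

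**4. Adjustment and effect size.** These need no arithmetic. Age, sex and co-morbidity are named for the primary Cox models only. The only factors named for the secondary test are period and network.

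**The case against.** The strongest reply is that the text does specify an interaction. It names a factorial version of the test and makes a significant interaction the criterion. That is correct. A reader might infer that the planned test would declare success on a shared trend or a stable difference between hospital groups. With no intervention effect, an ordinary four-group log-rank test does reject in about 86% of simulated runs when both hospital groups fall from 39% to 35%. But the article does not name a four-group test, those rates and the non-network cell size are assumed, and such a rejection would not satisfy a rule that requires an interaction favouring the network. The documents do not support the stronger reading.

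A reader might also infer that hospital is dropped between the primary and the secondary analysis. It is not, because the primary Cox models list no hospital term either. What goes unmet is the stated intent to evaluate effects in clusters.

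It can further be said that covariates, variance and reporting are details for a fuller analysis plan, and that the survival rates carried over from the primary analysis may be covariate-adjusted. The wording is ambiguous on the second point. However, the article fixes the type of test. A log-rank-type test works on observed times by group, adjusts at most through strata, and does not itself produce an estimate. That is a choice of method and can be improved, not only a missing detail.

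Finally, the analysis is secondary and the primary model is unaffected. This stands, and it limits the severity but not the value of a cheap change.

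**Conclusion.** The point holds as a weakness of method in the one comparison that protects against time trends. The plan intends an interaction, but names a family of tests whose ordinary forms do not test one. Even the favourable reading leaves the contrast unadjusted, blind to hospital and without an effect size.

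The only quantified part is the clustering: a false-positive rate of about 12-32% at nominal 5%, for a hospital-by-period SD of 0.10 to 0.20. It depends on that assumed SD, on 11 + 11 hospitals and on 1820 patients per cell. With no such variation the excess disappears. Confounding by patient mix cannot be sized from the article.

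**What to change.** In the Secondary analysis section, replace the log-rank test with one Cox model fitted to all four cells:

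- terms for period, network and period × network, with age, sex and co-morbidity as in the primary models
- stratification by hospital, which absorbs the network main effect and leaves the interaction estimable from within-hospital changes
- hospital-clustered variance with a small-sample correction, since there are only 11 network hospitals
- the interaction reported as a ratio of hazard ratios with 95% CI, and tested for the conclusion now tied to the log-rank test.

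The outcome data and basic covariates are already planned. The extra work is coding and a few sentences. One thing to confirm is that the anonymised insurance data carry a hospital code for the non-network hospitals too, because stratification and clustering need it.

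The interval will probably be wider. Under the assumptions above, the correct SE is 1.28 to 1.89 times the one that ignores hospital. Power falls accordingly from the simulated 90% at alpha 0.05 (72% at 0.05/6) for a fall from 39% to 32% in the network only, figures which assume no hospital variation.
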